## Abstract

**Background::**

New oral anticoagulants (NOAC) are gradually accepted by clinical practice for its convenient route of administration and stable effect. Both rivaroxaban and dabigatran etexilate have been used in the prevention and treatment of venous embolism after arthroplasty, but there is a lack of direct comparison between the 2 effects. Therefore, the purpose of this randomized controlled trial was to evaluate the efficacy and safety of 2 new oral anticoagulants, rivaroxaban, and dabigatran etexilate, in the prevention of venous thromboembolism after joint replacement.

**Methods::**

This is a prospective randomized controlled trial to study the efficacy and safety of rivaroxaban and dabigatran etexilate in the prevention of venous thromboembolism after joint replacement, and is approved by the clinical research ethics of our hospital. Patients were randomly divided into 1 of 2 treatment regimens:

Patients, doctors, nurses, and data collection assistants were blinded to group allocation. The indicators of observation include:

Data were analyzed using the statistical software package SPSS version 25.0 (Chicago, IL).

**Discussion::**

This study will evaluate the efficacy and safety of rivaroxaban and dabigatran etexilate in preventing venous thrombosis after joint replacement. The results of this experiment will provide clinical basis for the use of rivaroxaban or dabigatran etexilate to prevent venous thrombosis after joint replacement.

**Ethics and dissemination::**

Private information from individuals will not be published. This systematic review also does not involve endangering participant rights. Ethical approval was not required. The results may be published in a peer-reviewed journal or disseminated at relevant conferences.

**OSF Registration number::**

DOI 10.17605/OSF.IO/QVDCW.

## Introduction

1

Venous thromboembolism (VTE), one of the most common complications after joint surgery, which includes deep venous thrombosis (DVT) and pulmonary embolism (PE), is a complication that orthopedic surgeons must focus on its prevention and pay attention after surgery.^[1]^ The study showed that patients who did not receive medication had a 40% to 60% incidence of deep venous thrombosis and a 1% to 2% risk of pulmonary embolism.^[2]^ For the prevention of VTE, in addition to the commonly used physical prevention methods (such as the lower limb power pump to enhance muscle contraction), oral antithrombotic, and diffusion drugs are also one of the basic prevention methods, and have been recommended by domestic and foreign clinical practice guidelines.^[3,4]^

At present, the common anticoagulants in drug prevention are vitamin K antagonists (VKA), unfractionated heparin (UFH), low molecular weight heparin (LMWH), new oral anticoagulants (NOAC), etc.^[5]^ The enoxaparin, which represent the LMWH, is a classic drug to prevent VTE after major orthopedic surgery, but it is inconvenient for patients because of the daily subcutaneous injection.^[6]^ Therefore, in recent years, the new oral anticoagulant has attracted the attention of clinicians because of its high specificity and delicious clothing. NOAC include Xa factor inhibitors (e.g., rivaroxaban) and direct thrombin inhibitors (e.g., dabigatran etexilate), which have more advantages in their delivery routes, for anticoagulation will not be affected by food intake, and have little effect on interactions with other drugs, so there is no need for regular monitoring during medication. It is stable, and gradually accepted clinically.^[7,8]^

At present, rivaroxaban and dabigatran etexilate have been widely used in the prevention and treatment of venous embolism after joint replacement, and their clinical effects have been confirmed. However, few studies have directly compared the efficacy and safety of the 2 in the prevention and treatment of venous embolism after arthroplasty. Therefore, the purpose of this randomized controlled trial is to evaluate the efficacy and safety of 2 new oral anticoagulants, rivaroxaban, and dabigatran etexilate in the prevention of venous thromboembolism after joint replacement.

## Materials and methods

2

### Protocol register

2.1

This is a prospective randomized controlled trial to investigate the efficacy and safety of rivaroxaban and dabigatran in the prevention of venous thrombosis after joint replacement. We followed the Consolidated Standards of Reporting Trials (CONSORT) guidelines for reporting randomized trials and provided a CONSORT flow diagram (Fig. 1) and the Standard Protocol Items: Recommendations for Interventional Trials (SPIRIT) 2013 statement.

**Figure 1 F1:**
[figure not shown]
Flow diagram.

### Ethics and registration

2.2

This research program is in accordance with the Helsinki Declaration and approved by the Clinical Research Ethics Committee of our hospital. This protocol has been registered in open Science Framework (OSF) (Registration number: DOI 10.17605/OSF.IO/QVDCW). All patients need to sign a written informed consent before they are randomly assigned to continue the trial.

### Sample size

2.3

The aim of this prospective study was to explore a comparison of the efficacy and safety of rivaroxaban and dabigatran etexilate in preventing venous thrombosis after joint replacement. The exploratory of this study does not necessarily require formal sample size calculations. So, based on past clinical experience and previous studies,^[9]^ the sample size of 600 participants (300 in each group) was sufficient to achieve the actual purpose of the trial.

### Patients

2.4

Inclusion criteria: meet the criteria for elective joint replacement surgery (including shoulder, hip, knee, including trauma, or arthritis); no signs of embolism in venous color Doppler ultrasonography and pulmonary CT examination; all patients are the first time to underwent joint replacement.

Exclusion criteria:

(1)existence of severe coagulation dysfunction;(2)existence of cardiovascular and cerebrovascular diseases;(3)allergic to the drugs used in this experiment;(4)existence of severe immune dysfunction;(5)tumor or bone tuberculosis;(6)amalgamation of other systemic major diseases;(7)existence of other new oral anticoagulants contraindication;(8)unable to understand the research protocol after explanation or unwilling to participate.

### Study design

2.5

Eligible participants were randomly assigned to the rivaroxaban oral group or dabigatran etexilate oral group in a 1:1 ratio using a central network-based random tool. The random sequences are generated by SAS 9.3 software (SAS Institute, Cary, NC) by independent statisticians who do not participate in trial implementation or statistical analysis. Randomization was performed without any stratification. The clinical research coordinator entered participant information on the tablet and was given a random number. The research assistant obtained the allocation of participants from the computer. Throughout the study, the research assistant was responsible for screening, recruiting participants, and assigning random numbers to participants who had been included. Results evaluator was responsible for the evaluation of the scale. The grouping of personnel is unknown to all clinician, researchers, research assistants, participants, intervention supervisors, and statisticians who conduct statistical analysis. The drugs were distributed by unwitting nurses to patients with corresponding numbers according to the drug number.

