### Interventions

2.6

Before operation, the patients were examined by Doppler ultrasound to determine whether there was venous embolism, and if necessary, additional pulmonary CT was taken to rule out pulmonary embolism. The rivaroxaban group began to take 10 mg, once a day, 6 to 8 hours after operation, while the dabigatran etexilate group began to take 1 to 4 hours after operation, which was halved at the first time, and recovered to 220 mg once a day the next day. Both course of treatments lasted for 2 weeks.

Ultrasonic Doppler examination of limbs was performed by ultrasound doctors at 1 or 2 weeks after operation. If the formation of DVT is suspected, ultrasonic Doppler examination should be performed immediately; if pulmonary embolism is suspected, pulmonary CT or angiography should be performed in addition to ultrasonic Doppler examination, and the results should be recorded. The patients were followed up for 30 to 35 days after the last administration. Hematological examination was performed before operation, on the same day after operation and before discharge, and abnormal laboratory indexes were monitored. Hematological and imaging tests could also be performed during follow-up if necessary.

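### The all-roles blinding claim cannot hold as described for patients, nurses, treating clinicians and research assistants, because first-dose times and a one-arm dose change reveal the arm and the research assistant obtains the allocation

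*Protocol article*

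**What the plan says.** The blinding claim appears twice in the protocol article. The Abstract (Methods) says: "Patients, doctors, nurses, and data collection assistants were blinded to group allocation". Section 2.5 (Study design) goes further: "The grouping of personnel is unknown to all clinician, researchers, research assistants, participants, intervention supervisors, and statisticians who conduct statistical analysis". The masking device described there is a drug number, by which nurses who are said to be unaware of the group hand out the drug.

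Section 2.6 (Interventions) gives the two schedules. For one arm: "The rivaroxaban group began to take 10 mg, once a day, 6 to 8 hours after operation". For the other: "while the dabigatran etexilate group began to take 1 to 4 hours after operation", with a first dose "which was halved at the first time, and recovered to 220 mg once a day the next day". No dose change is stated for rivaroxaban. Neither section mentions a placebo, a dummy dose or matched packs.

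Section 2.5 also says: "The research assistant obtained the allocation of participants from the computer". Of the same role it says that "the research assistant was responsible for screening, recruiting participants, and assigning random numbers to participants who had been included".

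**The concern.** A drug number hides a label. It does not hide the hour at which a dose is given, or a change of dose from the first day to the second. If the two arms start at different times and nothing is given at the other arm's time, whoever gives, takes or charts the first dose can read the arm from the clock. Separately, section 2.5 says both that research assistants do not know the grouping and that the research assistant obtains it.

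This matters because some outcome data depend on staff judgement. Section 2.6 orders extra Doppler, CT or angiography when DVT or PE is suspected, and the findings feed the primary composite in section 2.7. The non-major bleeding list in section 2.7 includes wound hematoma judged excessive and surgical site bleeding, with no threshold for either, and it is open-ended. In a comparison of two active drugs, staff who can infer the arm may look for or record these events differently between arms. Readers would also rely on a blinding statement that the described conduct does not deliver.

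**Working it through.** The article gives no figure to reproduce on this point. The check is a comparison of intervals and a cross-reading of roles.

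**1. First-dose windows (section 2.6), in hours after operation**
- Dabigatran etexilate: [1, 4]. Rivaroxaban: [6, 8].
- Overlap = max(0, min(4, 8) − max(1, 6)) = max(0, 4 − 6) = 0 h.
- Smallest separation between a first dose in one arm and a first dose in the other: 6 − 4 = 2 h. Largest: 8 − 1 = 7 h.

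Without dummy dosing, the first-dose time alone identifies the arm for every patient dosed within the window.

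**2. Dose change (section 2.6)**
- Dabigatran etexilate: first dose halved, full daily amount from the next day.
- Rivaroxaban: no change stated.

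This is a second marker of the arm, independent of the clock. From the second day both arms take drug once daily, so dosing frequency adds nothing after that.

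**3. Which of the roles claimed as blinded do these facts reach?**

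| Role | Claimed blinded in | Fact against the claim |
|---|---|---|
| Patients | Abstract; 2.5 | Receive the first dose at an arm-specific time; can infer the arm if they know the schedule |
| Nurses | Abstract; 2.5 (as distributors) | Cannot give the first dose on schedule without knowing which window applies |
| Treating clinicians | Abstract (as doctors); 2.5 | Can see the time of the first dose and the dose change |
| Research assistants | 2.5 | Section 2.5 has this role obtain the allocation |
| Ultrasound doctors | Plausibly covered by the terms for doctors and clinicians | None: routine scan is at 1 or 2 weeks, and no access to dosing times is stated |
| Analysing statisticians | 2.5 | None: the cue arises at the bedside |

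**4. Is concealment of allocation affected?** Section 2.5 uses a central network-based tool and assigns numbers to participants already included. Nothing says that the assistant sees the allocation before inclusion. The conflict is therefore about blinding after assignment.

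**5. A related loose end.** Section 2.5 has the clinical research coordinator receive the random number, but the research assistant assign it and obtain the allocation. The text does not say whether the allocation means the treatment or only a code.

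**The case against.** The strongest reply is that this is a condensed article. A double-dummy schedule, with a dose at both times in both arms, could sit in the full protocol. The times in section 2.6 might describe only when active drug starts, and the allocation might be only a coded number. These readings are possible, so a reader who infers that the blinding simply does not exist goes beyond the text. They do not clear the point, however. The article makes an explicit claim for nearly every role beside a schedule that defeats it, and the drug number it offers does not mask a dosing time. Section 2.5 also already has a separate term for the random number, so the plain reading of allocation is the treatment group.

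Three further inferences are tempting and not supported:
- **That the ultrasound doctors were left out of the blinding lists.** The general terms for doctors and clinicians plausibly cover them.
- **That the statisticians are unblinded.** Nothing connects them to first-dose times.
- **That the recruiting assistant's access breaks allocation concealment.** Numbers go to participants already included.

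It is also fair to say that the primary outcome is only partly exposed. It includes all-cause mortality, and Doppler is scheduled for all patients. Only the additional imaging triggered by suspicion depends on bedside judgement, and the bleeding items cited are secondary safety outcomes. This limits the likely bias but does not make the blinding statement accurate.

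**Conclusion.** The point stands in a bounded form. As described, the blinding claim cannot hold for patients, nurses, treating clinicians and research assistants. For the first three, the reason is two windows with no overlap, at least 2 hours apart, plus a dose change in one arm only. For research assistants, it is a contradiction within section 2.5. The conclusion assumes that no dummy doses are given, that patients are dosed within the stated windows, that those concerned know the two schedules, and that the allocation obtained is the treatment group and not a code.

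It does not extend to the ultrasound doctors, the analysing statisticians or allocation concealment. I put no figure on the resulting bias. The article gives no expected event rates for the two arms and nothing on how knowledge of the arm would change recording, so any such number would be invented. The statement should be corrected even so, because it is a central validity claim, made twice, and the article's own schedule and role descriptions contradict it.

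**What to change.** Reconcile the Abstract (Methods), section 2.5 and section 2.6 in one of two ways:

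1. State the masking method that hides both the first-dose time and the dose change, if one is in use. The blinding claim can then stay for the bedside roles.
2. Otherwise, withdraw the claim for the roles that can infer the arm, and describe the trial as assessor- and analyst-blinded.

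In either case:
- Have the web tool return only a drug number to the recruiting assistant, and say whether the coordinator or the assistant receives it.
- State that the ultrasound doctors, the analysing statistician and whoever among existing staff classifies VTE and bleeding work without access to allocation or first-dose times. That classifier has to be named, because section 2.5 gives the results evaluator only the evaluation of a scale.

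The cost is wording and an access setting in the web tool. Under the second option the trial carries a weaker blinding label. The triggering of extra imaging and the recording of bleeding at the bedside also stay open to bias, and this should be stated as a limitation. No change to any dose or timing is proposed.

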### Interventions

2.6

Before operation, the patients were examined by Doppler ultrasound to determine whether there was venous embolism, and if necessary, additional pulmonary CT was taken to rule out pulmonary embolism. The rivaroxaban group began to take 10 mg, once a day, 6 to 8 hours after operation, while the dabigatran etexilate group began to take 1 to 4 hours after operation, which was halved at the first time, and recovered to 220 mg once a day the next day. Both course of treatments lasted for 2 weeks.

Ultrasonic Doppler examination of limbs was performed by ultrasound doctors at 1 or 2 weeks after operation. If the formation of DVT is suspected, ultrasonic Doppler examination should be performed immediately; if pulmonary embolism is suspected, pulmonary CT or angiography should be performed in addition to ultrasonic Doppler examination, and the results should be recorded. The patients were followed up for 30 to 35 days after the last administration. Hematological examination was performed before operation, on the same day after operation and before discharge, and abnormal laboratory indexes were monitored. Hematological and imaging tests could also be performed during follow-up if necessary.

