### Outcome measures

2.7

(1)Validity index: The primary outcome is a combination of total VTE (venography or symptomatic DVT and/or PE) and all-cause mortality during treatment, which is defined as the time from the date of the first study to 3 days after the last administration, and the secondary outcome is a combination of major VTE (venography or symptomatic proximal DVT and/or PE) and VTE-related mortality during treatment.(2)Security index: The main safety outcome is the incidence of massive hemorrhage from the first medication in the study to 2 days after the last use (continued treatment). Massive hemorrhage is defined as clinically fatal bleeding that occurs in critical organs (such as retroperitoneal, intracranial, intraocular, or intraspinal), requiring surgery, outside the surgical site, and associated with it. The secondary safety outcome was the incidence of clinically related non-major bleeding events, defined as polyphyly hemorrhage, accidental hematoma (>25 cm^2^), excessive wound hematoma, epistaxis (>5 min), gingival bleeding (>5 min), gross hematuria, rectal bleeding, cough or hematemesis, vaginal bleeding, semen bleeding, traumatic intra-articular bleeding, or surgical site bleeding, etc. Secondary safety outcomes also include the incidence of adverse reactions, such as abnormal laboratory indicators (with special emphasis on liver and kidney function indicators), allergic reactions, and other adverse events.

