### Statistical analysis

2.9

Data were analyzed using the statistical software package SPSS version 25.0 (Chicago, IL). Continuous variables were described as the mean ± standard deviation, and differences between groups were analyzed using a series of one-way analysis of variance (ANOVA) with Bonferroni's post-hoc test, while differences between groups over time were analyzed using multi-way ANOVA with Bonferroni's post-hoc test. Categorical variables were described as the number (%), and were analyzed by Fisher's exact test. A *P* value of <.05 was considered statistically significant.

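### Symptomless DVT is read at different times in different patients: the scheduled scan may fall at week 1 or week 2, and the primary window closes 3 days after the last dose

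*Protocol article*

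**What the plan says.** All references are to the Protocol article.

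- Scheduled imaging (2.6 Interventions): "Ultrasonic Doppler examination of limbs was performed by ultrasound doctors at 1 or 2 weeks after operation". The text does not say who chooses the week, on what basis, or with what tolerance.
- Unscheduled imaging (2.6): "If the formation of DVT is suspected, ultrasonic Doppler examination should be performed immediately". Suspected PE leads to CT or angiography as well.
- Treatment length (2.6): "Both course of treatments lasted for 2 weeks".
- Primary outcome (2.7 Outcome measures): "The primary outcome is a combination of total VTE (venography or symptomatic DVT and/or PE) and all-cause mortality during treatment". The period is "defined as the time from the date of the first study to 3 days after the last administration".
- Follow-up (2.6): "The patients were followed up for 30 to 35 days after the last administration". No scan is scheduled in that period; imaging is done only if necessary.
- Analysis (2.9 Statistical analysis): "Categorical variables were described as the number (%), and were analyzed by Fisher's exact test".
- Size (2.3 Sample size): 300 patients per arm, without event rates, effect size or power.

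**The concern.** A DVT without symptoms is known only from a scan, so the scan day decides which of these events can be seen. A week-1 scan comes halfway through the course and cannot show a symptomless DVT that forms in week 2. If some patients are scanned at week 1 and others at week 2, the reported proportion mixes two different quantities.

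The window adds a second difference. It follows the last dose, so a patient who stops early is observed for less time. A positive week-2 scan, or a death after the window has closed, is then not a primary event. Stopping happens after randomisation and, with anticoagulants, may follow bleeding. A comparison of simple proportions does not allow for unequal observation time.

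At stake is the primary outcome of a direct comparison of two drugs. A symptomless DVT that formed after a week-1 scan cannot be recovered at the analysis.

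**Working it through.** There is no figure in the plan to reproduce. The check has two parts: day arithmetic from the text, and the size under stated assumptions.

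**1. Which scheduled scan is inside the window**

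Inputs: operation on day 0; scans on nominal days 7 and 14 (2.6); window closes on last-dose day + 3 (2.7).

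| Last dose | Window closes | Week-1 scan counts | Week-2 scan counts |
|---|---|---|---|
| day 3 or earlier | day 6 or earlier | no | no |
| days 4–10 | days 7–13 | yes | no |
| day 11 or later | day 14 or later | yes | yes |

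A completer whose last dose is on day 13 or 14 has a window closing on day 16 or 17, which holds both scan days. A patient who stops on day 5 has a window closing on day 5 + 3 = 8. A positive scan on day 14, or a death on day 10, is not counted.

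**2. Events missed through week-1 scanning**

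Let p be the DVT rate by 2 weeks, L the share of it that appears after week 1, and s the share of patients scanned only at week 1. If every late event is symptomless:

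- observed rate = p × (1 − L × s)
- share missed = L × s

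With s = 0.5 (assumed), L = 0.2 gives 0.2 × 0.5 = 10%, and L = 0.4 gives 0.4 × 0.5 = 20%. At an assumed p = 10% and 300 per arm there are 0.10 × 300 = 30 DVTs, of which 3 to 6 are missed in each arm. If a share q of late events is symptomatic and caught by the immediate scan, the loss falls to L × s × (1 − q). PE and death inside the window do not depend on the scan day.

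**3. Power**

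Assumed true halving of risk, 300 per arm, two-sided 5%, normal approximation (Fisher's exact test is somewhat more conservative). Both rates are multiplied by 1 − L × s.

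| Scanning | Multiplier | 10% v 5% | 20% v 10% |
|---|---|---|---|
| all at week 2 | 1 | 64% | 93% |
| half at week 1, L = 0.25 | 0.875 | 58% | 89% |
| half at week 1, L = 0.5 | 0.75 | 51% | 83% |

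The last row uses a late share above the 20–40% range and is there as a harsher case.

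**4. Difference between arms with identical drugs**

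This arises only if something differs by arm; both splits below are assumptions.

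- Week-1 share 40% v 60%, p = 10%. L = 0.2: 0.10 × (1 − 0.08) = 9.2% v 0.10 × (1 − 0.12) = 8.8%, a difference of 0.4 points. L = 0.4: 8.4% v 7.6%, a difference of 0.8 points. The standard error with 300 per arm is √[(0.092 × 0.908 + 0.088 × 0.912)/300] = 2.3 points in the first case and 2.2 in the second, so the shift is about 0.2 to 0.4 standard errors.
- Early stopping before day 11 in 5% v 15%, with week-2 scans lost and p = 10%: 0.10 × 0.95 = 9.5% v 0.10 × 0.85 = 8.5%, a difference of 1.0 point in favour of the arm that stops more. This is again an upper figure, since it counts every DVT in early stoppers as lost.

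**The case against.** Several objections have force.

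- **Blinding.** A reader might infer that the scan rule biases the drug comparison. The documents do not support that. Section 2.5 states that clinicians, researchers, participants and the analysing statisticians do not know the allocation. If that holds, scan choice should be similar in both arms and the cost is lost events and power. The first-dose times after operation differ between the arms (2.6), which could reveal allocation, but the article may simply omit how this is handled, so nothing here rests on it. Blinding does not prevent arms from differing in early stopping when the drugs themselves cause it.
- **Size.** Even with a 40% v 60% split, the artificial difference is a fraction of a standard error.
- **Completers.** The window excludes a scheduled scan only after early stopping, and the article gives no stopping rate. An on-treatment window is also a stated choice, not a contradiction.
- **Symptomatic events.** Scans on suspicion catch these at any time, so 10–20% is a ceiling.
- **What counts.** Section 2.7 names venography or symptomatic DVT, while 2.6 schedules only Doppler. Read literally, a symptomless Doppler finding is not an event, and the scan day would hardly affect the primary outcome. This stands, and is itself something to reconcile.
- **Both weeks.** The scan rule might mean a scan in each week. The text does not say so, and that reading leaves the window problem for early stoppers.

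Two further inferences go too far. The start of the primary window is awkwardly worded, but the safety window in the same section runs from the first medication, so this is a wording query. And data from the later follow-up are not shown to be discarded: no efficacy outcome uses them, but late events may be reported as adverse events, for which 2.7 gives no end date. An efficacy outcome over follow-up would be an optional addition.

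**Conclusion.** The point holds as a defect in how the primary outcome is ascertained. As the article stands, symptomless DVT is read at week 1 in some patients and week 2 in others, and a week-2 scan does not count after a last dose on day 10 or earlier. Nothing elsewhere in the article repairs this.

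The expected harm is missed events, reduced power and a proportion that belongs to no defined time. Its size rests on assumptions: half the patients scanned at week 1 and 20–40% of 2-week DVT appearing later give a loss of at most 10–20% of DVT, less to the extent that late events are symptomatic. It also presumes that a symptomless Doppler finding counts. Bias between arms is possible but not shown; early stopping is the likelier route, because blinding does not prevent it.

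**What to change.** Amend sections 2.6 and 2.7 together:

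1. Set one scheduled scan time for every patient: the 2-week scan already allowed, with a stated tolerance. Keep the immediate scan on suspicion.
2. Count the primary outcome for all randomised patients to one fixed day that contains the scan and its tolerance, for example day 14 + 3 = 17, whenever the drug was stopped. Keep the on-treatment window as a supporting analysis.
3. State whether a symptomless DVT found on Doppler is a primary event, so that the two sections agree.

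With a common scan day and a common closing day, the artificial differences in the working disappear by design, apart from missing scans. The cost is mainly wording, plus return visits: some patients who would have been scanned at week 1 may have been discharged and must come back, and some of those scans will be missing. No change to dosing or treatment duration is implied. The change should be in place before scanning starts, because a week-2 scan that was not done cannot be replaced at the analysis.
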